### Part 1. Research participant information form

This section will compromise a legitimate description of the purpose of the study, the procedures to be followed whereby detailed information of the activities and examinations that will take place will be provided. Also, it will explain the risks and benefits of participating in the study, as well as the compensation and insurance of the study. The form will also include information regarding privacy and data protection, also it will mention that the study was reviewed and approved by the Ethics Committee of the ITM and the local authorities of DRC. Moreover, study participants (or guardians) will be informed that participation in the study is completely voluntary and can withdraw from the study at any time without any negative consequences. Details regarding the contact person in case of questions will be also given.

This study informed consent is based on individuals capable of giving informed consent. For those unable of giving informed consent, we ensure that a legally authorized representative of this person has given permission and this permission takes account of the participants previously formed preferences and values. Minors (<18 years old) are not allowed to participate in this study. Moreover, this study has requested and obtained the permission of the gatekeeper, in this case Zones de Santé (health district) to enroll clusters (healthcare center) during the field visit happened 1st May – 9th May, 2021. Lastly, no opt-out procedures will be stated as this research does not entail any biological residuals nor other type of remaining material such as audio-recordings.

### 5.3 Specific procedures and activities

In this section, the procedures for the measurements described in section 5.1 are presented. Additionally to the information found below, Standard operational procedures (SOPs) will be developed for each measurement adapted to the context.

#### Demographic characteristics

Baseline data will be collected at the beginning of the study by a 2-section questionnaire conducted by the health professional. Health professional will ask the questions and filled in the information provided by the participant. In section 1, the information to be gathered will include contact details (personal or relatives telephone number, email address, living address). This section of the questionnaire will always remain with the field staff, peer educators and healthcare professional, and will never be transferred into the data collection database nor shared with external bodies. Section 2 will include demographic characteristics of birthday, marital status, number of children, number of people living in the household, profession (also spouse), smoking (nonsmoker, former, or current), and frequency of alcohol consumption. All data collected by section 2 will be transferred to the database, pseudonymized directly and linked to the anonymized ID, to comply with EU GDPR and data protection regulations.

#### Adherence to a healthy lifestyle (primary outcome).

The healthy lifestyle adherence will be measured by a closed-ended multiple-choice questionnaire including questions regarding diet and physical activity. The questionnaire was developed in India by Dubasi and co-workers to assess the adherence to dietary and physical activity advice for weight control in lifestyle-related diseases. It was validated with 100 patients with non-alcoholic fatty liver and concluded to be a reliable and valid tool to assess adherence to lifestyle modification advice in lifestyle-related diseases. This tool comprises 14 questions, 12 regarding diet and 2 related to physical activity. Each question has 5 multiple choice answers (A, B, C, D, E). The answers to each question were weighted based on relevance and interest of this study, providing a minimum response of 1 and a maximum of 5 points (**Annex 6**). The score of each question is summed up providing a final score ranging from 14 – 65 points.

The questionnaire will be conducted by the health professional. Health professional will ask the questions and filled in the answer provided by the participant. When finished, the questionnaire must be checked by the health professional for completeness. Consequently, the answer per question will be entered by the data-entry into an excel template developed by the ITM for the calculation of the final score after each follow-up.

#### Anthropometrics

The anthropometric measurements will be carried out by the health professional following the guideline for the collection of physical measurements advised by the WHO STEPwise approach to non-communicable disease risk factor surveillance. These procedures entail the following:

### Height

It will be measured by using a UNICEF height measuring board positioned on a firm surface against a wall. The procedure will be the following:

1. Ask the participant to
  - Remove their shoes and headgear (hat, cap, hairs bows, combs, etc.)
  - Stand on the board facing you
  - Stand with feet together, heels against the backboard, and knees straight
  - Look straight ahead and not look-up
2. Make sure eyes are at the same level as the ears
3. Move the measuring arm gently down on to the head of the participant and ask the participants to breathe in and stand tall
4. Read the height in centimeters at the exact point to the nearest mm
5. Ask the participant to step away from the measuring board
6. Record the height measurement in centimeters

### Weight

It will be measured by a digital weight scale (SECA) placed on a firm, flat surface. The procedure will be the following:

1. Ask the participant to:
  - Remove footwear and socks. They should also take off heavy belts and empty their pockets of mobiles, wallets, and any other object.
  - Step on to scale with one foot on each side of the scale
  - Stand still, face forward, place arms on the side and wait until asked to step off
2. Record the weight in kg.

### BMI

This measurement will be calculated by the health professionals by using the formula  $BMI = \text{weight in kg} / \text{height in meters}^2$ . Also, the BMI will be calculated automatically in the excel template.

### Waist circumference

It will be evaluated with a constant tension tape (e.g. tape measure). Ideally, this measurement will be taken without clothing, directly over the skin. If not possible, the measurement may be taken over light clothing. Any thick or bulky clothing will be removed. The measurement should be assessed at the end of a normal expiration, with the arms relaxed at the sides, and at the midpoint between the lower margin of the last palpable rib and the top of the iliac crest (hip bone). The procedure will be the following:

1. Stand to the side of the participant, locate the last palpable rib and the top of the hip bone. You may ask the participant to assist you in locating these points on their body.
2. Ask the participant to wrap the tension tape around themselves and then position the tape at the midpoint of the last palpable rib and the top of the hip bone, making sure to wrap the tape over the same spot on the opposite side.
3. Ask the participant to:
  - a. Stand with their feet together with weight evenly distributed across both feet
  - b. Hold the arms in a relaxed position at the sides
  - c. Breathe normally for a few breaths, then make a normal expiration
4. Measure WC and read the measurement at the level of the tape to the nearest 0.1 cm, making sure to keep the measuring tape snug but not tight enough to cause compression of the skin

## 5. Record the measurement

### Clinical indicators

These measurements will be taken by the health professionals following the guideline for the collection of physical measurements advised by the WHO STEPwise approach to non-communicable disease risk factor surveillance .

### **Glycemia**

This biomarker will be measured as stated in the device instructions and with the equipment of device that measures glucose (Achat glucometer), a batch of sufficient reagent test strips, single-use lancets, gloves, cotton balls or swabs, and disposable container. The procedure will be the following:

1. Put on gloves
2. Remove a test strip, put it into the machine, and close the test strip box. The strips are sensitive to heat and humidity, so only take one strip at a time and close the box tightly
3. Rub and kneed a fingertip to help withdraw blood (rub the side of the participant's finger closest to the thumb)
4. Wipe or swab the fingertip by using a sterile swab.
5. Lance the massaged place on the fingertip with the lancing device
6. Allow a hanging blood drop to form without applying too much pressure
7. Carefully collect the blood with the capillary tube until the blood reaches the mark on the tube. Put the blood onto the test field without touching it
8. Give the participant a cotton ball to press on the puncture.
9. Wait for the measurement to be displayed. The results are usually displayed in mmol/L or mg/dL.
10. Record the result

### **Blood pressure**

It will be assessed by an OMRON (Digital automatic blood pressure monitor)

The procedure will be the following:

Applying the cuff:

1. Place the left arm of the participant on the table with the palm facing upward
2. Remove or roll up clothing on the arm
3. Select the appropriate cuff size for the participant
4. Position the cuff above the elbow so that the lower band is positioned 1-2 cm above the elbow joint
5. Wrap the cuff snugly on to the arm and securely fasten with the Velcro
6. Keep the level of the cuff at the same level as the heart during the measurement

Using OMRON

1. Refer to the operating instructions included with the device.
2. Switch the monitor on
3. The monitor will start measuring when it detects the pulse. The SBP and DBP readings should be displayed within a few moments (systolic above and diastolic below)
4. Record the reading.
5. Wait three minutes, then repeat steps 2-5 two times more, take the mean of the second and third readings.

## Dietary evaluation

### **Diet diversity**

The minimum dietary diversity for women (MDD-W) developed by the Food and Agriculture Organization of the United Nations (FAO) is a dichotomous population-level indicator of whether participants have consumed at least five out of ten defined food groups the previous day. The MDD-W is used as a proxy to describe one important dimension of women's diet quality (micronutrient adequacy) in national and subnational assessments.

The general ten groups are presented below (list of foods contained by each group is presented in section 2 of guideline) :

1. Grains, white roots and tubers, and plantains
2. Pulses (beans, peas, and lentils)
3. Nuts and seeds
4. Dairy
5. Meat, poultry, and fish
6. Eggs
7. Dark green leafy vegetables
8. Other vitamin A-rich fruits and vegetables
9. Other vegetables
10. Other fruits

The threshold of this tool is: > 5 groups of food groups consumed indicates better micronutrient adequacy. The interpretation compromises that groups of women of reproductive age where a higher proportion consume food items from at least five of the ten food groups are likely to have higher micronutrient adequacy than other groups that have a lower proportion of women achieving the threshold of food items from at least five food groups. In other words, women of reproductive age who consume food items from five or more of the ten groups are also highly likely to consume at least one animal-source food and either pulses or nuts/seeds and food items from two or more of the fruit/vegetable food group. The MDD-W would be assessed using a questionnaire model (**Annex 7**) and following the guidelines by the FAO. This questionnaire will be conducted and filled in by the health professional.

### Physical activity assessment

This assessment will be performed with the use of the International Physical Activity Questionnaire – (IPAQ) Short Form^28. This questionnaire compromises 7 questions and collects information on physical activity involvement on the domains of leisure time, domestic and gardening activities, and work-related and transport-related activities. Consequently, the Metabolic Equivalent (MET) per week will be calculated allowing to determine and classify the level of physical activity (low/medium/high) of the participant on a weekly basis. This questionnaire will be conducted and filled in by the health professional.

The questionnaire can be find at the following link <https://journals.plos.org/plosone/article/file?type=supplementary&id=info:doi/10.1371/journal.pone.0219193.s010>. The data will be analyzed according to the IPAQ guidelines presented in this link [https://www.physio-pedia.com/images/c/c7/Quidelines\\_for\\_interpreting\\_the\\_IPAQ.pdf](https://www.physio-pedia.com/images/c/c7/Quidelines_for_interpreting_the_IPAQ.pdf).

### **Acceptability of community-based strategies and intervention evaluation**

To explore the feasibility of complementing the intervention program with community-based activities, close-ended Likert scale questionnaires with an agreement scale (Strongly disagree [1], disagree [2], undecided [3], agree [4], strongly agree [5]) will be performed twice during the first year of intervention. The questionnaire will be provided by the health professional to the participant from the 3 healthcare centers in the intervention group and it should be filled in by the participant. Also during our field visit, the identification of potential partners to be involved in the community activities will be carried out (e.g. community leaders and representatives, regulatory authorities, government agencies, etc.).

If feasible and acceptable, activities engaging the community will be integrated into the intervention program delivered to the intervention group. These activities will be guided by designated volunteer community leader/s, preferably enrolled participants from the intervention group. The designated community leader/s will be in charge of organizing and promoting healthy lifestyle activities with support from the peer educators and other bodies involved. If acceptable, potential activities to be integrated are: deliver material to promote healthy lifestyle, promote physical activity sessions (e.g. walking pathway), sharing healthy cooking recipes and experiences, healthy lifestyle education involving children and husbands, etc. As mentioned, the feasibility of community-based activities will be assessed during the first year of interventions, in which also the type of community activities will be defined based on the needs and identified priorities by our target population.

As part of evaluating the feasibility of community-based activities but also to assess the intervention perception, focus groups with the participants per healthcare center of the intervention group will be carried out. The focus groups will provide the investigators' information regarding the perception of the intervention as well as identify needs (e.g. including husbands or children) and weaknesses that can be further addressed and improved. The focus groups will take place at each healthcare center of the intervention group every 6 months. All enrolled participants will be invited to participate in this activity by the peer educators and health professionals. Participants will be informed that this activity is completely voluntary, explained that the main objective is to discuss their perception regarding the intervention and to identify needs, weaknesses, and improvement points. Besides, participants will be informed about this activity before signing the ICF, where it will also emphasize that this activity is completely voluntarily, participation will have no impact in other related-activities to the intervention, and answers will remain anonymous. During the focus group, at each healthcare centers, all the attending participants will be divided into groups of a maximum of 10 people. Each group will have at least one moderator, a peer educator and/or healthcare professional, that will guide the questions, encourage discussion, and write down the most salient points of the discussion. The moderator will follow the focus group discussion (FGD) guide (**Annex 8**). After completion of each focus group, health professionals will synthesize this information and share it with the investigators for review.

## **5.4 Laboratory procedures**

Not applicable.

## **6. STUDY INVESTIGATIONAL PRODUCT**

### **6.1 Purchasing, preparation and administration**

Not applicable.

## 6.2 Participant compliance monitoring

Not applicable.

## 6.3 Prior and concomitant therapy

Not applicable.

## 6.4 Packaging

Not applicable.

## 6.5 Reception, storage, dispensing and return

Not applicable.

# 7. SAFETY ASSESSMENT

## 7.1 Adverse events

This is an intervention study with a low risk of adverse events as the intervention program compromises a lifestyle modification program through education and motivational strategies. The measurements to be taken are non-invasive, with the exception of blood glucose assess by blood sampling by using a finger prick. Moreover, the women participating in this study will be healthy (free of pre-existent severe conditions).

Concerning blood glucose measurement, its assessment will be performed by a health professional in a healthcare center and following the guideline developed by WHO STEPwise approach to non-communicable disease risk factor surveillance . The measurement will also be taken by following the instruction of the device, with required equipment (see section 5.3). Moreover, as participants do not have T2DM either GDM, blood glucose will be assessed randomly at any time, meaning no fasting state is required.

Nonetheless, this study has a low risk of participants, health professionals will ask participants for any symptom, indicator, or manifestation has arisen throughout the period intervention/measurements. This will be recorded in the written formats where all the measurements are being collected approximately every 6 months by the health professionals and followed though resolution if necessary.

## 7.2 Data and Safety Monitoring Board

As this study presents a low-risk for the participants, a Data and Safety Monitoring board is not required. The safety evaluation of the intervention program and measurements will be performed by the health professionals during the assessment of measurements (~ 6 months) as stated in section 7.1.

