#### 4.4 Randomization

We will use matched randomization to ensure that the two groups are balanced in terms of population size coverage and geographical area (urban/rural). This will be performed by manually creating 2 groups, each of 3 healthcare centers, based on their population size coverage and geographical area followed by randomly assign the intervention and comparison group to the 2 balanced groups. The randomization will be performed before the intervention begins and it will be carried out by ITM's staff.

Due to the nature of this research and the impossibility of masking the intervention program, this study will not be blinded. Anyhow, to ameliorate the risk of bias, the cluster randomization design was chosen to avoid contamination of information between the participants per healthcare center.

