## 5. STUDY PROCEDURES

### 5.1 Study/visit schedule

The data collection of this study will be carried out by at least 2 health professionals recruited from each healthcare center (a minimum of 12 health professionals, female if feasible). Previous to the intervention program, health professionals will receive a guideline with standardized procedures for the measurements, to ensure the accuracy of the measurements and high-quality data. **Table 1** describes the schedule of measurements including the demographic characteristics and also the primary and secondary outcomes presented in section 2.1 and 2.2. It includes as well the tool to be used and the person that will assess the measurement.

**Table 1.** Schedule of measurements and tools

|                                                              | Tool                          | Administered by                         | Baseline  | 6 months | 12 months | 18 months | 24 months |
|--------------------------------------------------------------|-------------------------------|-----------------------------------------|-----------|----------|-----------|-----------|-----------|
| Demographics                                                 |                               |                                         |           |          |           |           |           |
| Age                                                          | Close ended questionnaire     | Participant                             | X         |          |           |           |           |
| Marital status                                               |                               |                                         | X         |          |           |           |           |
| Number of children                                           |                               |                                         | X         |          |           |           |           |
| Profession                                                   |                               |                                         | X         |          |           |           |           |
| Smoking status                                               |                               |                                         | X         |          |           |           |           |

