| Physical activity                                            |                               |                                         |           |          |           |           |           |
| Physical activity questionnaire**                            | IPAQ-short version            | Health professional                     | X         | X        | X         | X         | X         |
| Acceptability of community support (only intervention group) |                               |                                         |           |          |           |           |           |
| Agreement scale questionnaire                                |                               | Health professional                     |           | X        | X         |           |           |
| Intervention assessment (only intervention group)            |                               |                                         |           |          |           |           |           |
| Focus groups                                                 |                               | Peer educators and health professionals |           | X        | X         | X         | X         |

Abbreviations: Body mass index (BMI); Type 2 diabetes mellitus (T2DM); Gestational diabetes (GDM) ; Minimum dietary diversity for women (MDD-W) In addition to these measurements, the ANC reports of pregnant women will be requested to the healthcare centers.

\*Primary outcome. \*\*Secondary outcome. †OMRON: Digital automatic blood pressure monitor. ~ 24-hour dietary recall will also be assessed randomly within the 6 month period, this will be performed by the health professional and by telephone. For pregnant women the weight will be compared to the recommended gain weight based on pre-pregnancy BMI, as follows: Underweight (BMI < 18.5): 13-18 kg; Normal weight (BMI 18.5 – 24.9): 11-16 kg; Overweight (25 - 29.9): 7-11 kg; Obese (BMI > 30): 5-9 kg.

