- Produced data: Data will be assessed for completeness, consistency, accuracy, and cleanness. Also the evolution of the primary and secondary parameters will be assessed based on % of women improving the lifestyle questionnaire score, % of women improving dietary habits and physical activity levels, % of women with a BMI <25 kg/m^2, % of pregnant women gaining the correct amount of weight based on their pre-pregnancy BMI, % of women with normal glycemia levels, and % of women with normal blood pressure.
- Intervention program indicators: this will be performed through summarizing the % of trained peer educator and health professionals, % of optimal data available for the primary and secondary outcomes, and the % of patients who have withdrawn from the study or loss to follow up.

Aside from quantitative quality controls, an intervention assessment based on focus groups of the participants will be carried out, as previously mentioned. These focus groups with the participants per healthcare center in the intervention group will take place every 6 months where the intervention perception, needs and weaknesses will be identified. Consequently, the information coming from this activity will be synthesized, reviewed and discussed by the investigators from Memisa and ITM, and take into account for further continuation of the intervention.

The local centers from Kisantu must allow the ITM's monitor or a monitor designated by the ITM, [name] and/or research assistant [name], access to any study-related files or source document present at the local center for external monitoring and control.

The sponsor will inform the Investigators concerned immediately upon notification of a pending study centers inspection by any regulatory authority or funder. Likewise, the investigator will inform the sponsor of any pending inspection.

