## 10. DATA MANAGEMENT

Data management procedures should comply with the ITM's [Research Data Management](#) and [Data Sharing Policy](#).

Data will be collected in standardized written forms by the health professionals approximately every 6 months. After each set of measurements, the data will be entered into a locked Excel template (developed by the ITM staff) by the data entry clerk where personal identifiers will be deleted and replaced by an anonymous ID number (pseudonymization) and coding techniques will be used for traceable information (e.g. date of birth or name of healthcare center) assuring participants confidentiality. The name and any other identifying detail will be retained at the recruitment site only and will NOT be included in any study data electronic file. After the data from the participants has been entered per set of measurements (~6 months), the data will be securely managed and transferred from Kisantu to the ITM following procedures stated in the data sharing agreement. After the ITM has received the data, data quality control and analyses will be performed by transferring the data from the locked Excel file into the statistical package of STATA/SE version 16 (see section 9). This procedure will be repeated after the initiation of the study with the demographic data and repeated approximately every 6 months until the completion of the study. After completion of the study, the complete database will be locked. Consequently, the final analyses (see section 8) will be performed, followed by sharing the results with local entities of Kisantu, Ministry of Health of DRC, and with the Congolese Center of Knowledge Management in Kinshasa, as well as a scientific report/paper will be drafted.

Data will be processed in accordance with the European General Data Protection Regulation (GDPR) and with the Belgian legislation on the protection of natural persons concerning the processing of personal data, this in collaboration with the Data Protection Officer (DPO's) working on Secure File Transfer Protocol (SFTP) from the ITM.

The Investigator will retain all source study-related documents for each for 20 years after completion of the study (see section 13).

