| Educational material                                       | -       | Topics above.                                                                                                                                                                                                                                                                                                      |
| Physical activity classes (intervention group)      |         |                                                                                                                                                                                                                                                                                                                    |
| Work-out sessions                                          | -       | Walking pathway
Aerobics class
Dancing class                                                                                                                                                                                                                                                                 |
| Setting goals (intervention group)                  |         |                                                                                                                                                                                                                                                                                                                    |
| Personal goals                                             | -       | Setting individualized dietary goals
Setting weight goals
Setting physical activity goals                                                                                                                                                                                                                    |
| Pedometer (intervention group)                      |         |                                                                                                                                                                                                                                                                                                                    |

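### Reported harms and birth outcomes are not named as coded variables or compared by arm, and safety is judged by centre staff who each see one arm only

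*Combined protocol and SAP*

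**What the plan says.** Section 7.2 (Data and Safety Monitoring Board) explains that the study is low risk and needs no board, and continues: "The safety evaluation of the intervention program and measurements will be performed by the health professionals during the assessment of measurements". Section 7.1 (Adverse events) has staff ask women about anything untoward and adds: "This will be recorded in the written formats where all the measurements are being collected approximately every 6 months by the health professionals". Events are then followed until resolved where necessary.

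On who these staff are, section 5.1 says: "The data collection of this study will be carried out by at least 2 health professionals recruited from each healthcare center". On allocation, section 4.4 describes two manually formed groups of three centres, "followed by randomly assign the intervention and comparison group to the 2 balanced groups".

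On data flow, section 10 says: "After each set of measurements, the data will be entered into a locked Excel template". The file then goes to the coordinating institute (ITM), whose staff run a quality check on all six centres about every six months (section 9). Of that check the protocol says: "Also the evolution of the primary and secondary parameters will be assessed based on % of women improving the lifestyle questionnaire score". The remaining indicators, here and in section 8.3.6, are diet and activity, BMI, gestational weight gain, glycemia, blood pressure, training, data completeness, and withdrawal or loss.

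On pregnancy, the note to Table 1 says that "the ANC reports of pregnant women will be requested to the healthcare centers". No variable or analysis is attached to those reports. Annex 3 gives work-out sessions and "Setting weight goals" to the intervention group only, and section 4.2 admits women in the first trimester.

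**The concern.** Whether a programme causes harm is a question about rates in two arms. The plan gives it to people who can each observe one arm, and it does not carry their written notes forward to the one place where both arms meet. A member of staff may well recognise a single injury that happened in a class. She cannot tell whether pregnancy losses, preterm births or falls are commoner than they would have been under basic education.

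Two things are at stake. An excess of such events could build up over 24 months without any planned step that sets the arms side by side. And the protocol's own statements could be neither supported nor contradicted by its data: that risk is low, and (section 11.5) that women will be told to expect no adverse effect on pregnancy, fetus or breastfeeding. The issue is whether harms are compared and by whom. It is not how often women are asked, nor whether a board should exist.

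**Working it through.** The plan states no figure on this point, so the main check is to trace the data.

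1. **Collection.** Symptoms are asked about and written on the measurement forms (7.1). Antenatal reports are requested (Table 1 note).
2. **Evaluator.** At least two professionals per centre (5.1), with allocation by whole centre (4.4). Each evaluator therefore has no comparator.
3. **Coding.** Section 10 has the forms keyed into Excel but names no harm field. It excludes none either. Section 8.2 lists the lifestyle score, anthropometry, glycemia, blood pressure, physical activity and diet diversity, and no harm or birth outcome.
4. **Six-monthly check.** The indicators in 8.3.6 and 9 include no adverse event, injury, pregnancy loss or birth outcome. The percentages are not said to be by arm.
5. **Final analysis.** Sections 8.3.1 to 8.3.6 contain no safety analysis. Section 8.3.4 applies the primary model to the secondary anthropometric, clinical and questionnaire outcomes.

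Result: glycemia, blood pressure and weight are compared between arms at the end. Reported harms and birth outcomes are compared at no stated step.

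What could 48 women per centre or 144 per arm (section 4.3) show? The documents give no event rates, so the rates below are assumptions.

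*No events seen.* The one-sided 95% upper bound is 1 − 0.05^(1/n), ignoring clustering:
- one centre, n = 48: 6.1%
- one arm, n = 144: 2.1%
- one arm at the 40 per centre used in the power calculation, n = 120: 2.5%

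*An assumed 2% against 5%.* A comparison centre expects 48 × 0.02 = 0.96 events and an intervention centre 48 × 0.05 = 2.4. By arm these become 144 × 0.02 = 2.9 and 144 × 0.05 = 7.2. Staff holding two or three events and no comparator could not recognise an excess. The two arm totals would at least prompt a question.

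*Would a test help?* Take effective n = 144 / (1 + 47 × ICC), two-sided 0.05, and power = Φ{[|p1 − p2| − 1.96 √(2p̄(1 − p̄)/n)] / √([p1(1 − p1) + p2(1 − p2)]/n)}, where p̄ is the mean of the two rates. The ICC of 0.1 is the plan's value for the lifestyle score. The value for events is unknown, so a range is shown.

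| ICC | Effective n per arm | Power, 2% v 5% | Power range, 1% v 3% to 10% v 20% |
|---|---|---|---|
| 0 | 144 | 0.28 | 0.23 to 0.66 |
| 0.01 | 144/1.47 = 98 | 0.21 | 0.17 to 0.50 |
| 0.1 | 144/5.7 = 25 | 0.08 | 0.07 to 0.17 |

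These use a normal reference and no loss to follow-up. With three centres per arm they are optimistic. Tabulation by arm is useful as description and not as a test.

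**The case against.** The case for leaving the plan alone has real content.

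- **Pregnancy-relevant measures are monitored.** A reader might infer that nothing related to pregnancy enters any check. The documents do not support that. Gestational weight gain, glycemia and blood pressure are in the six-monthly indicators. Section 2.2 treats glycemia as the indicator of diabetes and gestational diabetes. Clinical outcomes go into the mixed model (8.3.4), and 8.3.5 plans a subgroup analysis by pregnancy. This stands, but none of these measures would show an injury, a miscarriage or a preterm birth.
- **Harm is not invisible.** A reader might infer that no harm could be noticed. That also goes too far. Individual events are recorded and followed up, withdrawals are counted, the investigator may withdraw a woman on health grounds (4.5), and focus-group findings are reviewed every six months. What these do not supply is a comparison: focus groups run in the intervention arm only, and withdrawals are summarised without reasons or arm.
- **Pregnancy outcomes may be in hand.** The antenatal reports are requested and their content is not described, so it cannot be said that no pregnancy outcome is recorded. What is missing is a stated extraction and use.
- **A separate SAP is announced** (section 8) and could add a final table. True, but it can analyse only what was coded, and unless it also covered the six-monthly checks it would not help during the trial.
- **No board is proportionate** for an education programme. Agreed. Nothing here requires one.

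**Conclusion.** The point holds in a limited form. Reported symptoms, injuries, pregnancy losses and birth outcomes are not named as coded variables, and no stated check or analysis compares them by arm. The people assigned to evaluate safety each see one arm. An excess of these events under the programme would therefore not be picked up by any stated between-arm comparison, whereas worsening in glycemia, blood pressure or weight could be.

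The size is best given as a count: zero planned between-arm comparisons of reported harms or birth outcomes in 24 months and 288 women. The numerical illustration rests on assumed event rates and an unknown ICC for events. It shows that pooling sharpens what the data can exclude (6.1% to 2.1% with no events, before clustering), and that a significance test would usually be uninformative.

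The conclusion assumes that the forms and template hold no harm field beyond what section 10 describes, and that the announced SAP does not already provide one. It calls for a change that should be made before data collection starts. It does not undermine the primary comparison.

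**What to change.** 1. **Section 7.2.** State that centre staff record harms on the existing visit form, and that the entries are keyed into the existing Excel template as event, date and pregnant yes/no.
2. **Antenatal reports.** List the pregnancy outcomes to be extracted from the reports already requested, limited to those the reports contain (for example pregnancy loss, gestational age at delivery and birth weight, where available).
3. **Sections 8.3.6 and 9.** At each six-monthly check, the institute's staff, who already process all six centres, tabulate by arm and centre the women with any recorded harm and the pregnancy outcomes.
4. **Section 8.3 and the announced SAP.** Add a final descriptive table of harms and pregnancy outcomes by arm. Any interval should allow for centre and be presented as imprecise. Plan no formal test.

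The cost is a few template columns, a little more data entry, one table per check and some wording. No new staff, visits or procedures are needed. The columns must exist from the first visit, because events left only on paper may not be recoverable later.
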